### 2.9 Demographic characteristics

At baseline, participants provided information about their age, sex, race/ethnicity, educational attainment, household income, employment status and marital status.

### 2.10 Physical activity mediators and moderators

Hypothesized mediators and moderators of physical activity measured included: 1) a 4-item measure of Physical Activity Enjoyment adapted from a previous measure by Motl et al [23], 2) a 5-item measure of *Physical Activity Self-Concept *adapted from the Athletic Identity Measurement Scale [54], 3) the The 10-item Social Support for Exercise Behavior Questionnaire [55], 4) a 12-item version of the *Barriers Self-Efficacy Scale *[56], 5) a 13-item scale measuring the perceived benefits of physical activity adapted from [57], and 6) the 11-item short-form of the Center for Epidemiological Studies Depression symptoms scale [58].

### 2.11 Analyses

Mixed model regression (time within participant, unstructured covariance structure, restricted maximum likelihood estimation) will be used to test the hypothesis that KAM participants maintained kcal expenditure from baseline to 6,12, and 24 months, relative to a drop in kcal expenditure among the UC participants. Total and moderate kcal will be separately predicted from the time at which kcal was measured, which varies within participants, and randomized treatment group (KAM, UC), which varies across participants. This intent to treat approach will ensure that all available kcal observations, excluding those greater than 5 SD above median, from all randomized participants will be used to estimate model parameters.

For this report, 2-sided t-test, and chi-square statistics were used to compare the baseline characteristics of: 1) participants recruited for the study through direct mail versus self-referral; and 2) participants randomized to the intervention and control groups.

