### 2.8 Primary and secondary physical activity outcomes

The primary outcome measures for this study are kilocalories expended per week on a range of activities (total kcal/wk) and kilocalories expended per week on a subset of moderate and vigorous activities (moderate kcal/wk). Both kcal expenditure measures are computed using the CHAMPS instrument, designed for use in adult populations such as this one to assess the self-reported frequency and duration of a range of common activities and convert these reports into weekly kcal expenditure [50]. The CHAMPS instrument has demonstrated acceptable reliability with ICCs for moderate intensity activities of 0.67, 0.76, and 0.81–0.88 at six months, two weeks, and one week, respectively. Higher intensity activities demonstrate more modest ICCs of 0.66, 0.62, and 0.34–0.45 at six months, two weeks, and one week, respectively [51,52]. The instrument has also demonstrated adequate discriminate and construct validity, correlates well with other measures of physical activity and is sensitive to change [52].

Sample size was based on that which would be needed to detect a time (24 month vs. baseline observation) by treatment (KAM vs. UC) interaction at .80 power (two-tailed, alpha = 0.05) on the total kcal/wk variable in a two group repeated measures ANOVA. We assumed a common standard deviation of 1500 kcals/wk at each of 4 time points and a first order autoregressive residual covariance structure. These parameters suggested that N = 349 per study arm would be needed to detect the interaction of primary interest. Assuming non-differential 70% retention across study groups, we recruited N = 500 per arm.

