## 3. Results

Table 1 shows participant characteristics and physical activity level according to recruitment source; direct mail and self-referral. Participants who responded to a direct mailing about the study were less likely to be female and more likely to report "fair" or "poor" health status compared to those who self-referred themselves into the study after learning about the study through print, email or web media advertisement. No other statistically significant demographic or baseline physical activity characteristics differentiated direct mail and self-referral participants.

**Table 1 T1:** Participant Characteristics and PA as Mean and Standard Error or Percent by Source of Recruitment

	Direct Mail	Self-Refer	All
N	824	225	1049

age at baseline	57.1(.18)	57.2(.34)	57.1(.16)

female	69.5	82.7***	72.4

BMI, kg/m^2^	27.6(.19)	27.5(.38)	27.6(.17)

White	94.2	97.3	94.9

Hispanic/Latino	1.9	1.8	1.8

employed full time	76.2	79.1	76.8

4 year degree or more	66.3	68.4	66.7
			
functional health status fair or poor	7.0	3.1*	6.2

kcal/wk,	4721	4679	4712
total	(91)	(155)	(79)

kcal/wk,	2837	2731	2815
moderate or vigorous	(72)	(125)	(63)

moderate activity	23.5	28.4	24.6
30 minutes, 5/week			

vigorous activity	35.7	36.4	35.8
20 minutes, 3/week			

moderate or vigorous	48.8	55.1	50.1

* self-refer vs. mail, p < .05

*** self-refer vs. mail, p < .001

As documented in Table 2, at baseline the typical participant was about 57 years old, female, White, overweight (BMI ≥ 25 kg/m^2^), working full time, and college educated. Few participants reported fair or poor functional health status. Randomization successfully resulted in study groups that were similar on most demographic, physical activity, and psychosocial characteristics. The only observed demographic difference between the groups was that fewer KAM participants self-identified as White (95.6 vs. 92.4%, p < .05). Participants assigned to the KAM group were less likely to report engaging in moderate physical activity a minimum of five times per week, but reported higher levels of social support for physical activity from family members.

**Table 2 T2:** Participant Characteristics and PA as Mean and Standard Error or Percent by KAM and Usual Care Groups

	UC	KAM	All
N	526	523	1049

age at baseline	57.1(.22)	57.1(.22)	57.1(.16)

female	71.8	72.9	72.4

BMI, kg/m^2^	27.7(.24)	27.5(.23)	27.6(.17)

White	96.2	93.5*	94.9

Hispanic/Latino	1.2	2.5	1.8

employed full time	76.6	77.1	76.8

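### The primary mixed model, as described, leaves the baseline mean free in each arm; constraining the baseline means to be equal would regain precision and reduce the pull of a chance imbalance

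*Protocol article*

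**What the plan says.** - **Model (Section 2.11).** "Mixed model regression (time within participant, unstructured covariance structure, restricted maximum likelihood estimation) will be used to test the hypothesis" that KAM keeps its baseline kcal through 6, 12 and 24 months while UC declines. Total and moderate kcal are modelled separately. The named predictors are time of measurement and randomised arm. All available observations from all randomised participants enter, apart from extreme values. No baseline covariate and no equality constraint on baseline is named.
- **Contrast of interest (Section 2.8).** The trial was sized for a "time (24 month vs. baseline observation) by treatment (KAM vs. UC) interaction at .80 power (two-tailed, alpha = 0.05") on total kcal/wk, in a "two group repeated measures ANOVA". The inputs were "We assumed a common standard deviation of 1500 kcals/wk at each of 4 time points" and "a first order autoregressive residual covariance structure". The result: "These parameters suggested that N = 349 per study arm would be needed to detect the interaction of primary interest".
- **Estimand (Section 2.1).** Maintenance is defined relative to the participant's own baseline.
- **Timing (Sections 2.3 and 2.7).** The baseline interview was completed before randomisation.
- **Observed baseline (Table 2).** Total kcal/wk was 4781 (SE 114) in UC and 4643 (SE 109) in KAM. Moderate or vigorous kcal/wk was 2898 (SE 94) in UC and 2730 (SE 83) in KAM.

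**The concern.** Read together, these sections make baseline kcal one of four modelled responses, and the primary test a difference between arms in change from baseline. If each arm has its own baseline mean, the model estimates a baseline arm difference that is known by design to be zero in expectation, and subtracts it in full from the 24-month difference. This has two consequences.

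- **Precision.** The contrast carries baseline noise that an adjusted analysis would largely remove.
- **Chance imbalance.** Subtracting the whole baseline difference over-corrects whenever the correlation with follow-up is below 1. UC started higher on both primary measures, so partial regression to the mean in UC would look like the hypothesised UC decline.

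Precision is not in surplus here. The Table 2 standard errors imply a baseline SD for total kcal of 114 × √526 ≈ 2,615 in UC and 109 × √523 ≈ 2,493 in KAM, against 1,500 assumed for sizing.

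**Working it through.** **1. The plan's own figure.** The 349 per arm can be neither confirmed nor refuted, because Section 2.8 gives neither the effect size nor the autoregressive parameter. The inflation step does reproduce: 349 / 0.70 = 498.6, so 499 against the stated 500.

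**2. Information lost with complete data.** Assume a common SD σ at baseline and 24 months (as Section 2.8 does), n per arm, and correlation ρ between the two visits.

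- Change contrast: variance = 4σ²(1 − ρ)/n.
- Equal-baseline or baseline-adjusted contrast: variance = 2σ²(1 − ρ²)/n.
- Ratio (second to first) = (1 + ρ)/2, so the share lost = (1 − ρ)/2.

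The article states no 24-month correlation, so ρ is an assumption. The value 0.67 is the six-month ICC that Section 2.8 quotes for moderate-intensity activities. The value 0.20 is 0.67⁴ = 0.2015, that is, first-order autoregressive decay over four six-month steps. The value 0.50 lies between them.

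| ρ | Share lost | n per arm for the same power as 349 | Power at 349 per arm (planned contrast 0.80) |
|---|---|---|---|
| 0.67 | 16.5% | 349 × 0.835 → 292 | 0.87 |
| 0.50 | 25% | 349 × 0.75 → 262 | 0.90 |
| 0.20 | 40% | 349 × 0.60 → 210 | 0.95 |

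**3. With dropout.** The information matrix was computed for visits at 0, 6, 12 and 24 months, with assumed monotone retention of 90%, 80% and 70% at the follow-ups. The loss becomes about 13% (exchangeable correlation 0.67), 19% (exchangeable 0.50) and 32% (autoregressive in time, 0.67 per six months). With incomplete data the mixed model is no longer exactly a change-score analysis.

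**4. At the observed spread.** Take the pooled SD, 79 × √1049 ≈ 2,559, and 1049 × 0.70 / 2 ≈ 367 per arm. For 80% power at two-sided 5% (multiplier 2.80), the detectable difference is 2.80 × 2,559 × √(2(1 − ρ)) × √(2/367) for the change contrast. For the adjusted contrast, √(1 − ρ²) replaces √(2(1 − ρ)).

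- ρ = 0.67: 430 falls to 393 kcal/wk.
- ρ = 0.30: 626 falls to 505 kcal/wk.

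**5. Observed imbalance, UC minus KAM.**

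- Total: 4781 − 4643 = 138; SE = √(114² + 109²) = 158; z = 0.87, p = 0.38.
- Moderate or vigorous: 2898 − 2730 = 168; SE = √(94² + 83²) = 125; z = 1.34, p = 0.18.

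**6. Shift given that imbalance.** With equal SDs, the change contrast moves toward KAM by (1 − ρ) × difference.

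- Total: 0.33 × 138 = 46 (ρ = 0.67) to 0.80 × 138 = 110 (ρ = 0.20) kcal/wk.
- Moderate or vigorous: 0.33 × 168 = 55 to 0.80 × 168 = 134 kcal/wk.

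**7. Effect on error rates.** Over all randomisations, simulation of the change contrast under the null gave a mean of essentially zero and a type I error of 4.9–5.1%. Given the observed z, the null probability of a significant result favouring KAM is 1 − Φ{[1.96√(2(1 − ρ)) − (1 − ρ)z] / √(1 − ρ²)}. Over ρ = 0.20 to 0.67 this is 3.5–4.0% for total and 6.1–7.6% for moderate or vigorous kcal, against a nominal 2.5%. This assumes complete data and the same z among those analysed.

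**The case against.** - **The free baseline mean is inferred.** Section 2.11 neither writes out the interaction nor says how baseline is parameterised, and a fuller plan could specify the constraint. This stands as a caveat. The named predictors, the stated contrast and the definition of maintenance nevertheless make a difference in change the natural reading.
- **The planned test is valid.** A reader might infer that the analysis is biased in favour of KAM. The documents do not support that: the contrast is unbiased over randomisation and holds its type I error. The shift is conditional on a chance imbalance that is not significant on either primary measure.
- **The size is not a document figure.** The ICCs quoted are for intensity classes at six months, not for weekly kcal at 24 months. The low end of ρ is an extrapolation that the quoted reliabilities do not clearly support: they fall only from 0.76 at two weeks to 0.67 at six months, whereas geometric decay per fortnight would give 0.76¹³ ≈ 0.03. This stands, so the loss has to be given as a formula with an assumed range.
- **The shift cannot be scaled to a planned effect.** A reader might want to express it as a percentage of the difference the trial was designed to detect. Section 2.8 states no such difference.
- **The activity-recommendation outcomes.** Section 3 reports that "Participants assigned to the KAM group were less likely to report engaging in moderate physical activity a minimum of five times per week", and a reader might infer a bias against KAM on that outcome. The article does not say how these additional outcomes will be analysed, so there is no stated analysis to fault.

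**Conclusion.** The point holds as a weakness in efficiency and in behaviour given the observed baseline; it is not an invalid analysis. Under a common SD, some precision is lost for any ρ below 1. The loss is (1 − ρ)/2 with complete data, which is 16.5% to 40% over assumed ρ of 0.67 to 0.20, and about 13–32% under the one dropout pattern examined. Given the observed imbalance, the change contrast leans toward KAM by about 46–110 kcal/wk for total and 55–134 kcal/wk for moderate or vigorous activity. All of this rests on three assumptions: the arm-specific baseline reading of Section 2.11, similar SDs at baseline and 24 months, and values of ρ that the article does not supply.

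**What to change.** Keep the unstructured REML mixed model with all four visits as responses, and constrain the baseline mean to be equal across arms, with arm effects at 6, 12 and 24 months only. This retains all randomised participants and all eligible observations, and it still estimates change from baseline. It costs one line of model specification and uses data already collected. The article reports baseline data only and calls the trial ongoing, so the choice can be documented before outcomes are compared by arm.

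An alternative is to model the three follow-up visits with baseline kcal as a covariate interacting with time. It has a small cost: participants with no follow-up, or whose baseline value is removed by the extreme-value rule, drop out unless the value is imputed. That fits less well with the commitment in Section 2.11 to use every available observation.

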## 3. Results

Table 1 shows participant characteristics and physical activity level according to recruitment source; direct mail and self-referral. Participants who responded to a direct mailing about the study were less likely to be female and more likely to report "fair" or "poor" health status compared to those who self-referred themselves into the study after learning about the study through print, email or web media advertisement. No other statistically significant demographic or baseline physical activity characteristics differentiated direct mail and self-referral participants.

**Table 1 T1:** Participant Characteristics and PA as Mean and Standard Error or Percent by Source of Recruitment

	Direct Mail	Self-Refer	All
N	824	225	1049

age at baseline	57.1(.18)	57.2(.34)	57.1(.16)

female	69.5	82.7***	72.4

BMI, kg/m^2^	27.6(.19)	27.5(.38)	27.6(.17)

White	94.2	97.3	94.9

Hispanic/Latino	1.9	1.8	1.8

employed full time	76.2	79.1	76.8

4 year degree or more	66.3	68.4	66.7
			
functional health status fair or poor	7.0	3.1*	6.2

kcal/wk,	4721	4679	4712
total	(91)	(155)	(79)

kcal/wk,	2837	2731	2815
moderate or vigorous	(72)	(125)	(63)

moderate activity	23.5	28.4	24.6
30 minutes, 5/week			

vigorous activity	35.7	36.4	35.8
20 minutes, 3/week			

moderate or vigorous	48.8	55.1	50.1

* self-refer vs. mail, p < .05

*** self-refer vs. mail, p < .001

As documented in Table 2, at baseline the typical participant was about 57 years old, female, White, overweight (BMI ≥ 25 kg/m^2^), working full time, and college educated. Few participants reported fair or poor functional health status. Randomization successfully resulted in study groups that were similar on most demographic, physical activity, and psychosocial characteristics. The only observed demographic difference between the groups was that fewer KAM participants self-identified as White (95.6 vs. 92.4%, p < .05). Participants assigned to the KAM group were less likely to report engaging in moderate physical activity a minimum of five times per week, but reported higher levels of social support for physical activity from family members.

**Table 2 T2:** Participant Characteristics and PA as Mean and Standard Error or Percent by KAM and Usual Care Groups

	UC	KAM	All
N	526	523	1049

age at baseline	57.1(.22)	57.1(.22)	57.1(.16)

female	71.8	72.9	72.4

BMI, kg/m^2^	27.7(.24)	27.5(.23)	27.6(.17)

White	96.2	93.5*	94.9

Hispanic/Latino	1.2	2.5	1.8

employed full time	76.6	77.1	76.8

4 year degree or more	65.8	67.7	66.7

functional health status fair or poor	5.7	6.7	6.2

kcal/wk,	4781	4643	4712
total	(114)	(109)	(79)

kcal/wk,	2898	2730	2815
moderate or vigorous	(94)	(83)	(63)

moderate activity	27.8	21.4*	24.6
30 minutes, 5/week			

vigorous activity	35.0	36.7	35.8
20 minutes, 3/week			

exercise efficacy	4.59	4.59	4.59
all items	(.02)	(.02)	(.01)

support: family	2.73	2.82*	2.78
all items	(.03)	(.03)	(.02)

support: friends	2.60	2.65	2.63
all items	(.03)	(.03)	(.02)

enjoyment	4.12	4.08	4.10
	(.03)	(.04)	(.03)

PA Self-concept	3.86	3.84	3.85
	(.04)	(.03)	(.02)

PA self-efficacy	55.9	56.0	56.0
(1–100 scale)	(.79)	(.76)	(.55)

depression	0.35	0.38	0.36
mean of items	(.01)	(.01)	(.01)

* KAM vs. UC, p < .05

*** KAM vs. UC, p < .001

## 4. Discussion

This paper describes the design of the Keep Active Minnesota (KAM) trial and the baseline characteristics of the KAM intervention and usual care groups. This randomized controlled trial will evaluate the efficacy of a relatively low intensity phone and mail-based intervention designed to promote *maintenance *of physical activity among 50–70 year old adults who have recently increased their physical activity level. It may seem counterintuitive to expend effort to help those who have already initiated greater physical activity on their own maintain those efforts. However, just as smoking cessation is frequently not accomplished with a first attempt, so too, attempts to sustain a healthy level of PA may require multiple attempts. Moreover, even highly active individuals experience lapses in the face of high risk situations [59] and those who have recently increased their physical activity level may be particularly vulnerable during the period of time that it takes for them to move from initiating a new behavior to it becoming a well-established behavior or habit. Providing a modest level of effort to assist such individuals may well yield benefits that are more than commensurate with the effort expended. For some, it may be additional information or help in problem solving that will help to take them through this period. For others, it may simply be having an external agent who they know is working on their behalf, and to whom they feel a sense of connection or accountability that may do the trick – sustaining them in their efforts while they develop the skills to problem solve and overcome the inevitable barriers to physical activity.

To enroll in the trial, participants had to have increased their physical activity level during the past year to a minimum of 30 minutes of moderate or vigorous PA a day at least 2 days per week. Maintenance of this relatively modest physical activity level has the potential to yield important health benefits. Including improvements in functional capacity, fasting insulin levels, and reduce risk of Type 2 diabetes [33-35]. Although all KAM participants were required to meet the two day per week threshold, there was considerable variability in the frequency and intensity of reported physical activity. Subgroup analyses will examine whether the KAM intervention is differentially effective based on baseline physical activity level and physical activity history; secondary analyses will also be informative with respect to the dose of physical activity necessary for weight maintenance in this population.

Since most randomized trials of physical activity interventions focus primarily on initiation, with attention paid to maintenance when the novelty of the intervention may have worn off and adherence may be declining, recruitment to a maintenance-focused intervention provides an opportunity to engage people during the time period when they may be otherwise vulnerable to lapses in physical activity. Both the content and delivery of the KAM intervention were tailored for addressing maintenance. Telephone-based counseling has an increasing evidence base [60] and may be particularly suitable for a maintenance-focused intervention given that it is a flexible and relatively lower intensity intervention. The KAM intervention is also based on a theoretical model specifically developed to address issues related to PA maintenance which integrates principles of Bandura's Social Cognitive Theory (SCT) [47] and relapse prevention theory [61]. Intervention strategies were weighted heavily toward self-management, including cognitive (goal setting, identification of barriers and problem solving), behavioral (self-monitoring through use of pedometers & log-books, use of environmental cues), and environmental (phone coach support, development and leverage of social support) strategies.

Strengths of the KAM trial are its unique focus on maintenance, implementation of theory-based intervention and the use of phone- and mail-based delivery mechanism which due to its relatively low cost may lead to a high potential for dissemination if the intervention is shown to be efficacious over the long term. Limitations of the KAM study include the ability to generalize to a broad population of adults given the focus on 50–70 year olds and limited racial/ethnic diversity of the study sample. Although the intervention appealed to a large number of those eligible to enroll in the study, multiple strategies are needed to assure the broad population penetration needed to increase overall population levels of PA. Despite these limitations, the KAM study offers an innovative approach to the perennial problem of physical activity relapse. By focusing explicitly on physical activity maintenance, the KAM intervention holds considerable promise for modifying the typical relapse curve.
